**Results:**

The recruitment of study participants and data collection was undertaken from June 2018 to May 2019. Data and laboratory analyses are ongoing and are expected to be completed by December 2020. A total of 150 participants were enrolled, and 146 completed the study. We hypothesized that protein intake from animal-sourced foods in recommended quantities could support normal weight and length gain and lower the risk of undernutrition associated with similar amounts of plant-based protein. However, higher protein intake, especially from milk protein, may be linked to increased body fat via plasma amino acids and the growth hormone-IGF axis.

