### Study Outcomes

#### Primary Outcome

The primary outcome measure will be the conditional change of growth parameters (WAZ, WLZ, LAZ) from 6-12 months of age.

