### Statistical Analysis

There are two main parts of the statistical analysis. First, we will summarize the population characteristics of milk feeding, complementary feeding, and prevalence of undernutrition, overweight/obesity, and iron deficiency. Second, we will examine the associations between protein intake and source during complementary feeding and the outcomes specified in the objectives and hypotheses. All statistical tests will be considered significant when the *P* value is <.05 or 95% CIs of odds ratios do not include 1.

Descriptive data will be presented as mean (SD), median with interquartile range, or percentages depending on data type and distribution. These data will include demographic characteristics of infants and families, breastfeeding rate, age of the first introduction of complementary feeding, details of complementary feeding and energy/nutrient intake at each time point, average growth parameters at each time point, growth trajectory, and the prevalence of malnutrition (including wasting, stunting, overweight/ obesity, iron deficiency, iron deficiency anemia).

Protein intake at each time point, both total and separated by dietary source (ie, dairy protein, nondiary animal-based protein, and plant-based protein), will be considered as primary predictors to examine associations between protein intake and outcomes. To investigate associations between those predictors and continuous outcomes such as growth z-scores, percentage of body fat/fat-free mass, and blood parameters, we will use linear regression and correlation models (Pearson or Spearman correlation) for either univariate or multivariate analysis. For multivariate analysis, covariates will be selected for each of the dependent outcomes from previous research publications and our univariate analyses. Additionally, we intend to apply the directed acyclic graphs identifying covariates to reduce confounders [33]. If the dependent outcomes are categorical data such as nutritional status or iron status, binary or logistic regression analysis will be used as the main models.

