The study aims to reduce the bias of baseline body size of individual infants on growth outcomes by using conditional growth. This method captures how an individual child deviates from the average growth trajectory in the population, taking into account overall regression to the mean, and expresses growth acceleration or deceleration in an individual relative to this population growth pattern. For example, if the conditional weight z-score is positive, we can interpret that the infant has shown more rapid weight gain than others in the population who had the same baseline size [34]. Therefore, the conditional change in growth parameters from 6 to 12 months will be calculated using linear regression of weight/length z-scores at 12 months on baseline values at 6 months. Residuals from the model represent the difference between observed and predicted growth over this period.

We will use data from the standard recommendations, previous research, and our own data to determine the most appropriate cut-offs for low or high protein intake. We will then compare the outcomes between these groups.

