### Sample Size Calculation

We used the two-different means formulae [35] to calculate the sample size required to detect a 0.5 SD difference in growth parameters (WAZ, WLZ, and LAZ) between infants who receive red meat frequently and less frequently from 6-12 months of age (Textbox 2).

Sample size calculation.Mean difference 0.5 SDSD 1.0 (adopted from Olaya G et al [36])Power 80%, significance level .05Sample size: 126 participantsWith surplus 15% drop out rate, the final number is 148 participants

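### Regressing conditional-growth residuals on protein intake without 6-month size in the second step shrinks a true association by (1 − ρ²); a single baseline-adjusted model avoids this at no cost

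*Protocol article*

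**What the plan says.** The Primary Outcome section states: "The primary outcome measure will be the conditional change of growth parameters (WAZ, WLZ, LAZ) from 6-12 months of age". BMIZ is treated the same way as a secondary outcome.

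Statistical Analysis describes two steps.

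- **Step 1.** Conditional change "will be calculated using linear regression of weight/length z-scores at 12 months on baseline values at 6 months". Intake is not in this regression. The article adds: "Residuals from the model represent the difference between observed and predicted growth over this period". The declared purpose is to remove the influence of each infant's starting size.
- **Step 2.** Protein intake at each time point, in total and by source, "will be considered as primary predictors to examine associations between protein intake and outcomes". For continuous outcomes, "we will use linear regression and correlation models (Pearson or Spearman correlation) for either univariate or multivariate analysis". For the multivariate models, "covariates will be selected for each of the dependent outcomes from previous research publications and our univariate analyses", supplemented by directed acyclic graphs.

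Six-month size is neither named as a covariate in step 2 nor excluded from it. The article gives no correlation between intake and 6-month size.

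**The concern.** Step 1 removes baseline size from the outcome but not from the exposure. If intake is related to 6-month size, the step-1 slope on baseline absorbs part of what belongs to intake. The step-2 slope is then not the baseline-adjusted association that conditional growth is meant to deliver.

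Some relation is plausible. Larger infants may eat more, and intake per kg, the scale of the Thai reference intake cited in the Introduction, has weight in its denominator. The article does not say which scale the predictor uses, and the two mechanisms pull in opposite directions. The sign of ρ does not matter for the shrinkage because ρ enters squared, but its size is unknown.

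All three primary indices are affected. The design power is 80%, and enrolment and follow-up are complete, so lost power cannot be recovered by recruiting more infants.

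**Working it through.** **The plan's own sample size.** Inputs from Sample Size Calculation: difference 0.5 SD, SD 1.0, power 80%, significance level .05, for a comparison "between infants who receive red meat frequently and less frequently from 6-12 months of age". A two-sided test and equal groups are assumed; neither is stated. Per group: 2 × (1.960 + 0.842)² × 1.0² / 0.5² = 62.8, so 63, or 126 in total, as stated. With 15% dropout, 126 / 0.85 = 148.2, against 148 stated. On completion: "A total of 150 participants were enrolled, and 146 completed the study".

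**Shrinkage with intake as the only predictor.** Let B be the 6-month z-score, L intake (both standardised, correlation ρ) and Y the 12-month z-score, with Y = γB + βL + e.

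- Step 1: the slope of Y on B alone is γ + βρ, so the residual is R = β(L − ρB) + e.
- Step 2: the slope of R on L is β(1 − ρ²).
- One model, Y on L and B, gives β.

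Applied to the design difference of 0.5 SD, with 63 per group and SD 1.0 taken as the residual SD (an assumption):

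| ρ (assumed) | 1 − ρ² | Two-step estimate of 0.5 SD | Power, two-step | Power, one model |
|---|---|---|---|---|
| 0 | 1.00 | 0.500 | 80.1% | 80.1% |
| 0.1 | 0.99 | 0.495 | 79.3% | 79.7% |
| 0.2 | 0.96 | 0.480 | 76.9% | 78.5% |
| 0.3 | 0.91 | 0.455 | 72.4% | 76.3% |
| 0.4 | 0.84 | 0.420 | 65.4% | 73.0% |
| 0.5 | 0.75 | 0.375 | 55.8% | 68.1% |

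Power also falls in the one-model column because intake and baseline overlap. That is the honest price of adjustment. The two-step method falls further.

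Simulation with n = 146, an assumed 6-to-12-month slope of 0.7 and true β = 0.17 per SD of intake (5,000 runs) gave two-step means of 0.169, 0.154 and 0.128 at ρ = 0, 0.3 and 0.5. The single model gave 0.170, 0.170 and 0.171. Power at ρ = 0.5 was 58% against 69%.

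**No true association, intake alone.** With β = 0 the formula gives 0, so there is no bias. The two-step test is conservative: its t statistic has SD √(1 − ρ²), which is 0.866 at ρ = 0.5, so rejection is about P(|Z| > 1.96/0.866) = 2.4%. Simulation gave 2.6%, against 5.3% for the single model.

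**A covariate added at step 2 only.** Let Z have effect θ on growth and correlations r_BZ with B and r_LZ with L. With β = 0, R = θ(Z − r_BZ·B) + e, and the step-2 coefficient of L is

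−θ · r_BZ · (ρ − r_BZ·r_LZ) / (1 − r_LZ²).

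With θ = 0.3, r_BZ = ρ = 0.4 and r_LZ = 0.16: −0.3 × 0.4 × (0.4 − 0.064) / 0.9744 = −0.041. With θ = −0.3 it is +0.041. Simulation gave −0.041 and +0.043, and the single model about 0.

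Simulated two-step type I error with β = 0 and n = 146, against about 5% for the single model (all inputs assumed):

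| ρ and r_BZ | θ | r_LZ | Residual SD | Type I error |
|---|---|---|---|---|
| 0.3 | 0.2 | 0 | 0.6 | about 5% |
| 0.4 | 0.2 | 0 | 0.6 | about 8% |
| 0.5 | 0.3 | 0 | 0.6 | about 30% |
| 0.5 | 0.3 | 0.5 | 0.6 | about 12–13% |
| 0.5 | 0.3 | 0.5 | 1.0 | about 8% |

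**Baseline entered at step 2.** Regressing R on L and B gives the same coefficient for L as regressing Y on L and B. In simulation the two agreed to rounding error.

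**The case against.** The strongest reply is that the failing model is inferred. The article says how the conditional score is computed, not that 6-month size is kept out of the association model. Its covariate rule, including the directed acyclic graphs, could bring 6-month size in, and the residual model would then equal the single model exactly. Final covariate lists are commonly left to a fuller document that is not shown.

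This stands in part: the rule permits the remedy. It does not require it, and it cannot reach the univariate regressions and the correlations, which have no place for baseline. One route in the rule also works against it. By construction the residual is uncorrelated with the 6-month z-score of the same index, so a univariate screen against the conditional score would never select that z-score. Authors working with residuals may also reasonably believe that baseline is already dealt with.

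The objection on size stands. The article gives no ρ, random error in recalls and food records would lower the observed value, and below ρ = 0.3 the loss is under 9%.

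A reader might infer that the protein association is biased whenever intake is related to 6-month size, or that false positives approach 30%. Neither follows. With intake alone a null association stays unbiased and a real one is only pulled towards zero. The 30% case needs a residual SD of about 0.6 and a covariate unrelated to intake, neither of which comes from the article, whose sample size uses SD 1.0.

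**Conclusion.** The point holds as a conditional one. The procedure described attenuates a true protein association by (1 − ρ²) if intake correlates with 6-month size and baseline is absent from the second step: about 1%, 9% and 25% at ρ = 0.1, 0.3 and 0.5. Adding covariates related to both baseline size and growth at the second step only can bias the estimate in either direction and inflate type I error, by an amount that rests entirely on assumed correlations and residual SD.

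The documents do not support saying that the primary result will be distorted, because ρ is unknown and the covariate rule leaves room for 6-month size. The argument also does not extend to body composition: those outcomes are not residualised, so adding a 6-month index there would be a separate question.

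This is a worthwhile, free improvement to a stated method. It addresses only the residualising step, not confounding or error in measuring intake.

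**What to change.** For each of WAZ, WLZ and LAZ, and for BMIZ, state that the protein association will be estimated in one model:

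12-month z-score = protein predictor(s) + 6-month z-score of the same index + chosen covariates.

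The protein coefficient is then read as the association with conditional growth. Equivalently, state that the 6-month z-score will be entered in every model that has the residual as its outcome. Keep the conditional-growth residuals for description and plots, and do not base inference on simple correlations of the residual with intake.

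The cost is a sentence or two of wording. The data are already collected, the software and interpretation are unchanged, the required sample size does not move, and power for a true association was equal or higher in every intake-only case above.

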### Sample Size Calculation

We used the two-different means formulae [35] to calculate the sample size required to detect a 0.5 SD difference in growth parameters (WAZ, WLZ, and LAZ) between infants who receive red meat frequently and less frequently from 6-12 months of age (Textbox 2).

Sample size calculation.Mean difference 0.5 SDSD 1.0 (adopted from Olaya G et al [36])Power 80%, significance level .05Sample size: 126 participantsWith surplus 15% drop out rate, the final number is 148 participants

## Results

Recruitment commenced in June 2018 and was completed in October 2018. Data collection was completed in May 2019. Laboratory analyses are ongoing and are expected to be complete by December 2020. Initially, 150 infants were enrolled, and only 4 (3%) had dropped out at the end of the data collection period. The results of this study will be presented and disseminated through peer-reviewed journals and academic conferences.

## Discussion

Thailand has highlighted early life nutrition as a window of opportunity to overcome the double burden of malnutrition [37]. Several campaigns from the Thai government have been launched to improve maternal and infant nutrition. Examples include a program that encouraged supplementation of Triferdine, which consists of iron, iodine, and folic to women of child-bearing age, promotion of exclusive breastfeeding until 6 months of age as well as iron supplementation of infants and young children aged 6 months to 2 years [38]. However, there is no specific campaign related to complementary feeding and, to the best of our knowledge, no recent studies in this field.

Although recommendations should ideally be based on experimental data, the lack of recent data on dietary protein intake and growth outcomes in Thai infants precluded the development of a practical intervention that could be tested in a randomized controlled trial in this population. To address this issue, we decided to adopt a sequential approach in 3 consecutive studies, beginning with a descriptive study to gather information on the attitudes, knowledge, and practices related to complementary feeding in Thai families. This study provided a clearer picture of complementary feeding among Thai parents and highlighted interesting findings that were used in the design of the current prospective cohort study [39]. For example, rice porridge and mashed banana were the most common first foods for Thai infants with or without a small amount of egg yolk. Some Thai parents delayed providing animal-sourced foods to their children and had concerns that such foods were difficult to digest and had high allergenicity compared with plant-based proteins.

The second phase of our research consists of the observational study described here, incorporating the findings of our previous study. The aim is to investigate the intake of different protein sources during complementary feeding and associations between protein intake and growth outcomes, body composition and iron status in the same population, as well as to investigate possible mechanisms related to those associations. The results of this study may be used to plan the third phase of our research, testing an intervention to improve growth and iron status in this infant population.

## Abbreviations

BMIZ: body mass index z-score
CBC: complete blood count
DBM: double burden of malnutrition
ESR: erythrocyte sediment rate
IGF-1: insulin-like growth factor I
IGFBP-3: insulin-like growth factor-binding protein III
LAZ: length-for-age z-score
WAZ: weight-for-age z-score
WLZ: weight-for-length z-score
